#### Control group

The control group is receiving a dietary meal plan based on healthy eating recommendations in accordance with WHO guidelines. According to WHO, a healthy diet contains at least 400 g of fruits and vegetables, excluding potatoes, sweet potatoes, cassava, and starchy roots. A consumption of legumes, nuts, and whole grains (wheat, maize, millet, oats, rice, rye) is also promoted, as well as an intake of less than 5 g of salt per day, less than 10% of total energy intake from free sugars and less than 30% of total energy intake from fats, giving preference to unsaturated fats [55].

#### Outcome measures

The primary PRO of interest for this study are pain, fatigue, quality of sleep, quality of life, GI symptoms, and the presence of inflammation. To determine the effect of dietary intervention on the disease, the following questionnaires are being included:
Revised Fibromyalgia Impact Questionnaire (FIQR) [56], to verify the impact of FM on the patient’s life;Visual analog pain scale (EVA_Pain) [57], validated by Boonstra and colleagues [58], and brief pain inventory (BPI) to assess pain [59], validated by Keller and colleagues [60];Visual analog scale from a list of common gastrointestinal and extraintestinal symptoms in FM, IBS, and non-celiac gluten sensitivity (NCGS) to assess GI symptoms [61], validated by Bengtsson and colleagues [62];Short Form 36 (SF-36) [63], to check the quality of life, validated by Fredheim and colleagues [64];Validated Fatigue Severity Survey (FSS) [65], to check the fatigue level;Validated Pittsburg Sleep Quality Index (PSQI) [66], to check the quality of sleep.

Additionally, serum high-sensitive CRP (hs-CRP), Erythrocyte Sedimentation Rate (ESR) and Interleukin-8 (IL-8) are being measured to assess the presence of inflammation. The serum collection and hs-CRP and ESR analysis is being perfomed by *Joaquim Chaves Saúde* Laboratory, an external entity. The biomarker IL-8 quantification is being performed according to ImmuliteR© (Siemens, Germany) manufacturer’s protocol. Details on collection, laboratory evaluation, and storage of IL-8 is presented on Additional file 4.

Data on age, physical activity, and anthropometric parameters, such as waist circumference, height, and weight, are also being collected. Body composition, specifically fat mass, lean mass, and water, is being assessed by bio-impedance, through the scale of Inbody brand, model 770.

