### Sample size

In order to define the sample size required for the study and to give a statistical power of 80%, G-Power Software version 3.1.9.4 revealed that, for a desirable effect size of 50%, a minimum sample size of 45 individuals is required. In order to prevent follow-up losses, the target sample size is *n* = 100.

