### Statistical analysis

Baseline demographic and clinical characteristics of the participants of both groups will be analyzed using descriptive statistics. For the continuous normal distributed variables, the t-student test will be used to assess the association between the disease evaluation parameters, the inflammatory markers, and the dietary intervention. Correlations between variables will be sought at the different assessment moments. Regression coefficients will be calculated to determine the contribution of the domains for each variable. ANOVA will be used to evaluate the participants’ evolution within each group.

Missing data will not be included in the statistical analysis. Participants who discontinue or deviate from intervention protocols, as well as patients who meet exclusion criteria at some point of the intervention period, will be excluded. Motive of exclusion will be the outcome to be collected from these participants.

Statistical analysis will be performed using IBM SPSS Statistics Software, version 19.0. A *p* value of 0.05 is considered statistically significant.

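### Six unranked primary domains, ten measures and a flat 0.05: if any one significant result counts as a positive primary finding, the false-positive risk is well above 5%, by an amount that depends on an unstated correlation

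*Protocol article*

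**What the plan says.** All references are to the protocol article.

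- **Outcome measures** sets the primary tier: "The primary PRO of interest for this study are pain, fatigue, quality of sleep, quality of life, GI symptoms, and the presence of inflammation". It gives no order among the six and describes no secondary tier.
- The same section lists the instruments. Pain has two, EVA-Pain and the BPI. GI symptoms have a symptom-list scale ("Visual analog scale from a list of common gastrointestinal and extraintestinal symptoms in FM, IBS, and non-celiac gluten sensitivity (NCGS) to assess GI symptoms"), quality of life has "Short Form 36 (SF-36) [63], to check the quality of life", fatigue has "Validated Fatigue Severity Survey (FSS) [65], to check the fatigue level", and sleep has the PSQI. Inflammation has three markers: hs-CRP, ESR and IL-8. The FIQR is also listed ("Revised Fibromyalgia Impact Questionnaire (FIQR) [56], to verify the impact of FM on the patient’s life"), but it is not tied by name to any of the six domains.
- **Abstract, Methods** has the questionnaires completed at baseline, at 1 month and at 3 months. **Intervention** describes blood collection at the first visit and after 3 months only. Neither section says which time point is primary.
- **Statistical analysis** uses Student's t test for the disease parameters and the markers alike, and a p "value of 0.05 is considered statistically significant". It mentions no adjustment, testing order or requirement that several outcomes succeed together.
- **Sample size** says that "for a desirable effect size of 50%, a minimum sample size of 45 individuals is required", without saying which outcome this refers to.

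**The concern.** The choice of primary outcome is a protocol decision, and this protocol makes it: six domains, all primary, all judged at 0.05. With two pain measures, three markers and two post-baseline questionnaire times, no single result is marked as the one that answers the trial's question. A report could follow the plan to the letter and present whichever measure crossed 0.05 as a positive primary result.

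Two things are at stake. The error rate attached to a positive primary finding would no longer be the 5% that the threshold suggests. And the result to be headlined could be chosen after the data are seen, in a trial where, according to Study setting, the researchers know the allocation.

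**Working it through.** **The plan's own figures.** The document states no familywise error rate; 0.05 is its only error figure. Its sample size of 45 names no outcome, test, sidedness or alpha. Reading the effect size as 0.5 SD, a two-sided independent t test at 0.05 with 80% power needs 64 per group, so 45 does not reproduce under that reading. This is a separate matter, and nothing below depends on it.

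**Inputs**

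| Input | Value | Source |
|---|---|---|
| Primary domains | 6 | Outcome measures |
| Questionnaires or scales | 7 (FIQR, EVA-Pain, BPI, EVA-GI, SF-36, FSS, PSQI) | Outcome measures |
| Markers | 3 (hs-CRP, ESR, IL-8) | Outcome measures |
| Post-baseline times, questionnaires | 2 (1 and 3 months) | Abstract, Methods |
| Post-baseline times, markers | 1 (3 months) | Intervention |
| Threshold | 0.05, taken as two-sided | Statistical analysis; sidedness assumed |
| Correlation between test statistics | not given; 0, 0.5 and 0.9 shown | assumption |

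**Number of tests, k**

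- One score per domain: k = 6.
- Every listed measure once: k = 7 + 3 = 10.
- Adding the 1-month questionnaires: k = 7 × 2 + 3 = 17.

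**Independent tests.** P(at least one p < 0.05 | no true effect) = 1 − 0.95^k.

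- k = 6: 1 − 0.735 = 0.265
- k = 10: 1 − 0.599 = 0.401
- k = 17: 1 − 0.418 = 0.582

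**Correlated tests.** Take k two-sided normal tests with common correlation ρ, each written as √ρ·U + √(1−ρ)·E, with U shared by all tests and E specific to each. With c = 1.96,

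P = 1 − ∫ φ(u) [Φ((c − √ρ·u)/√(1−ρ)) − Φ((−c − √ρ·u)/√(1−ρ))]^k du,

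integrated numerically:

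| k | ρ = 0 | ρ = 0.5 | ρ = 0.9 |
|---|---|---|---|
| 6 | 27% | 21% | 11% |
| 10 | 40% | 29% | 13% |
| 17 | 58% | 39% | 15% |

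If the FIQR is left out because it has no named domain, k = 9 gives 37% at ρ = 0 and 27% at ρ = 0.5.

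**Cost of the two remedies in power.** Two-sided t test, difference 0.5 SD, 50 per group (the target of 100 split equally):

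- alpha 0.05, one primary outcome: 69.7%
- alpha 0.05/6 = 0.0083, six co-primaries: 42.8%

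Both figures are before losses to follow-up.

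**The case against.** The strongest reply is that the protocol never says that one significant result makes the trial positive. Its stated aim is to analyse effects on several named parameters. If each domain were reported as its own question, with no overall claim, the need for familywise control would be less clear-cut. The adjustment method and the choice of score are also often left to an analysis plan, which is not shown here. The first part stands as a condition on the finding: the inflation applies if any one result may carry the primary claim. It does not remove the finding, because the protocol itself fixes six unranked primaries and a flat threshold, and nothing in it prevents that use. A later plan would have to override this text as well as fill a gap.

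Four stronger readings are tempting, and the document does not support them.

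- **That the false-positive risk is 21% to 40%.** This takes a correlation between 0 and 0.5 as fact. Two pain scales and three inflammation markers in the same patients may well correlate. At 0.8 to 0.9, six to ten tests give about 11% to 17%, which is still at least twice 5%.
- **That there are 20 tests.** This doubles the blood markers, for which only one post-baseline collection is described. The text supports 17. The 1-month questionnaires themselves appear only in the abstract, and the schedule figures are not available.
- **That the sample size was computed for a single test.** The Sample size section names no test or outcome. All that can be said is that the figure is not tied to one.
- **That all ten measures belong to declared primary domains.** The FIQR does so only by inference.

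**Conclusion.** The concern holds in conditional form. The protocol makes six domains primary without ranking and judges the results at 0.05 with no hierarchy or adjustment. If any one significant result is reported as a positive primary finding, the chance of at least one false positive under no true effect lies well above 5% at every correlation examined. It runs from 11% (six tests, correlation 0.9) to 40% (ten independent tests), and up to 58% if the 1-month questionnaires are counted and all 17 tests are independent. The test counts come from the document. The correlation, the two-sided reading and one score per questionnaire are assumptions; analysing subscales or single symptom items would add tests. Because this affects the trial's main claim, it should be settled before outcome data are analysed by group.

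**What to change.** Before any outcome data are analysed by group:

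1. Name one primary outcome, with one score and one time point, compared between groups at two-sided 5%. A pain score at 3 months is one candidate, since pain is already a declared primary domain. The FIQR total is another, provided the sponsor states that it represents overall disease impact, because it is not now tied to any declared domain.
2. Make the remaining domains secondary, with one pre-named score each and Holm adjustment across them.
3. Label the 1-month results, the correlations and the regressions exploratory.
4. Tie the Sample size section to the chosen outcome.
5. Record the date of the choice and that it was made before group results were seen. Trials status says the trial is under way, and the researchers are not blind to allocation, so a late and undocumented choice would carry its own selection risk.

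The change needs no extra patients, visits or data. Its cost is that only one outcome can support the headline claim. At 0.5 SD with 50 per group, that outcome has about 70% power before losses, which is below the 80% aimed for. Splitting alpha six ways would leave about 43% for each outcome.

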#### Patient and public involvement

Patients or members of the public were not involved in the design, conduct, reporting, or dissemination of the research.

### Statistical analysis

Baseline demographic and clinical characteristics of the participants of both groups will be analyzed using descriptive statistics. For the continuous normal distributed variables, the t-student test will be used to assess the association between the disease evaluation parameters, the inflammatory markers, and the dietary intervention. Correlations between variables will be sought at the different assessment moments. Regression coefficients will be calculated to determine the contribution of the domains for each variable. ANOVA will be used to evaluate the participants’ evolution within each group.

Missing data will not be included in the statistical analysis. Participants who discontinue or deviate from intervention protocols, as well as patients who meet exclusion criteria at some point of the intervention period, will be excluded. Motive of exclusion will be the outcome to be collected from these participants.

Statistical analysis will be performed using IBM SPSS Statistics Software, version 19.0. A *p* value of 0.05 is considered statistically significant.

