**Methods:**

A sample of 100 female patients diagnosed with FM, followed up at Portuguese Institute of Rheumatology (IPR) in Lisbon, is being randomly allocated in two groups. Patients in the intervention group are adopting an anti-inflammatory diet, characterized by the exemption of the intake of foods containing gluten, dairy, sugar, and ultra-processed foods, during 3 months. During the first month, a low fermentable oligo-, di-, and monosaccharides and polyols (FODMAPs) diet is implemented, along with the anti-inflammatory diet, followed by the reintroduction of all fruits and vegetables over a consecutive period of 2 months. Patients in the control group are adopting a diet based on general recommendations for healthy eating. The outcomes are pain, fatigue, quality of sleep, quality of life, gastrointestinal symptoms, and inflammation. Before and after the 3 months intervention, and also 1 month after beginning the intervention, the following questionnaires are applied: Revised Fibromyalgia Impact Questionnaire, visual analog pain scale, Brief Pain Inventory,visual analog scale from a list of common gastrointestinal and extraintestinal symptoms in FM, Short Form 36, Fatigue Severity Survey, and Pittsburg Sleep Quality Index. Ultra-sensitive serum C-reactive protein, eritrocyte sedimentation rate, and interleukin-8 are determined. Age, physical activity, anthropometric parameters, and body composition are being collected. Student’s *t* test will assess the association between the disease evaluation parameters, the inflammatory markers, and the dietary interventions.

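### The inflammatory markers are assigned to a normality-dependent t test with no stated baseline adjustment; a prespecified log-scale ANCOVA on the M0 value would be firmer and more efficient

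*Protocol article*

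**What the plan says.** The Outcome measures section of the protocol article counts inflammation among the primary outcomes: "The primary PRO of interest for this study are pain, fatigue, quality of sleep, quality of life, GI symptoms, and the presence of inflammation". That makes six domains. The same section says which measurements carry this one: "serum high-sensitive CRP (hs-CRP), Erythrocyte Sedimentation Rate (ESR) and Interleukin-8 (IL-8) are being measured to assess the presence of inflammation". According to the Intervention section, blood is taken at the first meeting (M0) and again after 3 months, so each marker has a baseline value.

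The Statistical analysis section names one test for relating the outcomes, inflammatory markers included, to the diet: "For the continuous normal distributed variables, the t-student test will be used". It is limited to variables that are normally distributed. The abstract's Methods paragraph gives the same assignment without that limit: Student's t "test will assess the association between the disease evaluation parameters, the inflammatory markers, and the dietary interventions".

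The other methods named are correlations, regression coefficients and ANOVA. The ANOVA does not compare arms: "ANOVA will be used to evaluate the participants’ evolution within each group". The correlations and regression coefficients are given without a treatment contrast. On significance the text says only that a p "value of 0.05 is considered statistically significant"; whether tests are one- or two-sided is not stated. No SD, distribution or expected skew is given for any marker.

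**The concern.** The two statements lead to different analyses. A reader of the abstract would run t tests on all three markers. A reader of the Statistical analysis section would first have to decide, marker by marker, whether the data are normal. The method for a primary domain then depends on the data, and the Study setting section says that the researchers know the allocation.

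Concentrations and rates that cannot fall below zero are commonly right-skewed. On the raw scale a few high values then inflate the variance, and a proportional reduction becomes harder to detect. In addition, neither statement says that the M0 value is used to reduce residual variance, although it is already being collected. At stake are power and freedom from analyst discretion for the serum measurements that represent inflammation.

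**Working it through.** **The plan's own figure.** The Sample size section gives a minimum of 45 for 80% power at an effect size of 50%. It is not tied to any marker, so there is no marker-specific power to reproduce. Read as d = 0.5, a two-sided independent t test needs 64 per arm, so 45 is not reproduced. That is a separate sample-size matter and is not part of this point.

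**Inputs.** From the article: target of 100 and alpha 0.05. Assumed: 50 per arm, two-sided tests, lognormal markers, a ratio of geometric means of 0.6, log-scale SD s and baseline correlation r.

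**Analyses on the log scale, checked by formula.** With n per arm, z = (d / k) × √(n/2), where d = |ln 0.6| / s, k = 1 without baseline adjustment and k = √(1 − r²) with ANCOVA. Power ≈ Φ(z − 1.96), and √(50/2) = 5.

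- s = 1.0, t test on logs: d = 0.511, z = 0.511 × 5 = 2.55, Φ(0.59) ≈ 0.72. Simulated: 71%.
- s = 1.0, r = 0.6, ANCOVA on logs: k = √(1 − 0.36) = 0.8, z = 2.55 / 0.8 = 3.19, Φ(1.23) ≈ 0.89. Simulated: 88%.
- The same with r = 0.5 (k = 0.866): z = 2.95, power ≈ 0.84. With r = 0.7 (k = 0.714): z = 3.58, power ≈ 0.95.

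**Raw-scale tests, by simulation at the same setting.**

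| Analysis | Power |
|---|---|
| t test, raw 3-month values | about 53% |
| t test, raw change from M0 | about 41–42% |
| Mann-Whitney | about 69–70% |
| t test, log 3-month values | about 71% |
| ANCOVA, log values with log M0 | about 88% |

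The gap of 88 − 53 = 35 points splits into 71 − 53 = 18 from the log scale and 88 − 71 = 17 from the baseline.

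**Skew alone.** Here the log-scale effect is held at d = 0.5 so that only skew varies (50 per arm).

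| Log SD | Raw t | t on logs | Loss (points) |
|---|---|---|---|
| 0.3 | 0.69 | 0.71 | 2 |
| 0.5 | 0.65 | 0.70 | 5 |
| 0.8 | 0.57 | 0.70 | 13 |
| 1.0 | 0.51 | 0.70 | 19 |
| 1.2 | 0.45 | 0.70 | 25 |

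With no true effect, the raw t test rejects in 3.8% to 5.3% of runs at 45 or 50 per arm.

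**Baseline alone.** At d = 0.5 and r = 0.6, z rises from 2.5 to 2.5 / 0.8 = 3.125. Power by the formula goes from Φ(0.54) ≈ 0.71 to Φ(1.165) ≈ 0.88; simulation gives about 70% and 87%. This gain does not depend on skew.

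**The normality check.** The article does not name one. If Shapiro-Wilk were used on a single arm of 50, it would reject in about 57% to 59% of samples at log SD 0.3, 92% to 93% at 0.5, and nearly always from 0.8 upwards. With mild skew, the choice of method would be close to a coin toss.

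**The case against.** The strongest reply is that this is a condensed article. Its normality qualifier shows that the authors expected some variables to be non-normal, and a fallback is something that a full protocol or SAP commonly holds. This stands. A reader might infer that skewed markers have no planned group comparison, but the article alone cannot show that.

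A reader might also infer that skewed markers will be put through a low-power raw t test. Under the Statistical analysis section a non-normal marker would not go to the t test at all. That reading rests only on the abstract, where a dropped condition may be ordinary shortening.

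Nor does the text establish that the t test ignores M0: it does not say whether 3-month values or changes are compared. What can be said is that no baseline adjustment is stated. At the central setting (log SD 1.0, r = 0.6), both raw readings fall well below log-scale ANCOVA.

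Three points on size also stand. The whole gap from 53% to 88% must not be credited to skew, since ANCOVA would help a normal variable too. Holding the ratio at 0.6 while log SD runs from 0.8 to 1.2 also moves the standardised effect from 0.511 / 0.8 = 0.64 to 0.511 / 1.2 = 0.43, so a power range produced that way is not a pure skew effect. And exclusion of other inflammatory diseases could trim high values, so mild skew is possible.

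Finally, a prespecified rank test would also remove the dependence on normality. It would recover most of the loss from skew, but not the gain from the baseline.

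**Conclusion.** The point holds in a limited form. For one of six primary domains, the article names a between-group test that is conditional on normality in one place and unconditional in another, and it states no baseline adjustment. The method then turns on a data-dependent check, and the named test is less efficient than a comparison that the collected data already allow.

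Under the central assumptions the raw t test has about 53% power against about 88% for log-scale ANCOVA, with log scale and baseline contributing about equally. If log SD is only 0.3 to 0.5, the loss from skew is 2 to 5 points and the gain is almost wholly from M0 adjustment, about 70% to 87% at d = 0.5 and r = 0.6. Skew, correlation and effect size are all assumptions, because the article gives none of them. The cost is in power and discretion; false-positive error is not inflated. This is a cheap improvement rather than a flaw that invalidates the comparison.

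**What to change.** In the Statistical analysis section, replace the t test for these markers with wording such as: *The 3-month log-transformed hs-CRP, ESR and IL-8 values are compared between groups by ANCOVA with the log M0 value as covariate, and reported as ratios of geometric means with 95% confidence intervals. No normality pre-test chooses the method.* Bring the abstract's Methods paragraph into line. If a fuller plan already fixes a rule for non-normal markers, reconcile it with this wording.

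The change costs analysis wording only and needs no new data, since M0 blood is already drawn. The small downside is that results are ratios rather than differences in the original units.

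### The diet effect rests on a t test with no baseline covariate, and change over time is tested only within each arm; one baseline-adjusted between-group model should replace both

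*Protocol article*

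**What the plan says.** The protocol article's Statistical analysis section assigns the comparison of the diets, for normally distributed continuous variables, to one method: "the t-student test will be used to assess the association between the disease evaluation parameters, the inflammatory markers, and the dietary intervention". The Abstract (Methods) repeats that Student's t "test will assess the association between the disease evaluation parameters, the inflammatory markers, and the dietary interventions". Neither place names a baseline covariate, says whether the test is applied to final values or to change, or names the visit.

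The time course is handled separately: "ANOVA will be used to evaluate the participants’ evolution within each group". Regression is mentioned for another purpose: "Regression coefficients will be calculated to determine the contribution of the domains for each variable". No group-by-time term and no joint between-group model of the visits is stated.

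The data would support such a model. According to the Abstract, the questionnaires are completed before and after the 3 months "and also 1 month after beginning the intervention". The Intervention section has blood drawn at M0 and again after 3 months.

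Two further sentences in Statistical analysis limit which data are used. One is "Missing data will not be included in the statistical analysis". The other excludes a class of patients: "Participants who discontinue or deviate from intervention protocols", together with those who come to meet an exclusion criterion.

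**The concern.** The aim is comparative: the diet against healthy-eating advice. The only stated method that follows patients across visits works inside one arm and cannot answer that question. Both arms receive nutrition consultations, a meal plan and regular telephone contact, and the Discussion allows that the control diet may itself help. Improvement in both arms is therefore plausible, and a pair of within-arm p values can easily differ by chance.

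Two things are at stake. The first is power, because a t test on final values, or on change, uses the baseline score less well than a model that adjusts for it. The second is interpretation, because a significant change in the diet arm beside a non-significant change in the control arm is easily mistaken for a diet effect.

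**Working it through.** **Inputs from the protocol article.** Target of 100 patients in two groups (Abstract, Sample size); significance level 0.05 (Statistical analysis); effect size given as 50% and power 80% (Sample size).

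**Assumptions.** 50% means a standardised difference d = 0.5; 50 per arm; two-sided test; equal SD at both visits. The correlation r between baseline and follow-up is not in the document, so a range is shown.

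**The plan's own figure.** The Sample size section states a minimum of 45 individuals. A two-sided two-sample t test at d = 0.5 needs 64 per arm for 80% power, so the 45 is not reproduced under this reading. That is a separate matter, and nothing below depends on it.

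**Step 1: power of the between-group test.** The effect in units of the relevant SD is:
- final values: 0.5
- change: 0.5 / √(2(1 − r))
- baseline-adjusted (ANCOVA): 0.5 / √(1 − r²)

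At r = 0.5, for example, change gives 0.5/√1 = 0.50 and ANCOVA gives 0.5/√0.75 = 0.577. At r = 0.6 they give 0.5/√0.8 = 0.559 and 0.5/0.8 = 0.625. Two-sample power from the noncentral t distribution, 50 per arm (the degree of freedom spent on the covariate is ignored):

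| r | t test, final values | t test, change | ANCOVA | n per arm for 80%: final / change / ANCOVA |
|---|---|---|---|---|
| 0.3 | 69.7% | 55.3% | 73.7% | 64 / 89 / 59 |
| 0.5 | 69.7% | 69.7% | 81.6% | 64 / 64 / 49 |
| 0.6 | 69.7% | 79.0% | 87.2% | 64 / 52 / 42 |
| 0.7 | 69.7% | 89.2% | 93.4% | 64 / 39 / 34 |
| 0.8 | 69.7% | 97.5% | 98.5% | 64 / 27 / 24 |

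The ordering does not depend on the values chosen. The ANCOVA variance factor 1 − r² = (1 − r)(1 + r) never exceeds 1 (final values) or 2(1 − r) (change), since 1 + r ≤ 2.

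**Step 2: what the within-arm tests can show when the diets do not differ.** The plan was simulated 10,000 times with 50 per arm, three visits, correlation 0.5 between visits, the same true change in both arms (half of it reached at 1 month), and a repeated-measures ANOVA in each arm at 0.05.

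| True change at 3 months, both arms (SD) | Significant in exactly one arm | Significant in diet arm only |
|---|---|---|
| 0.1 | 16% | 8% |
| 0.2 | 35% | 17% |
| 0.3 | 50% | 25% |
| 0.4 | 42% | 21% |
| 0.5 | 20% | 10% |

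In the same runs the between-arm t test on 3-month values was significant in about 5% of trials, as it should be. The one-arm-only rate is close to 2p(1 − p), where p is the power of one within-arm test. At a change of 0.3 SD, p = 0.452 and 2 × 0.452 × 0.548 = 0.495. These rates apply to each outcome, and Outcome measures lists seven questionnaires and three blood markers.

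**Step 3: which rule loses the 1-month scores.** Leaving out missing values could mean using whatever is available at each visit, which would keep a 1-month score. The sentence that excludes patients who discontinue or deviate removes them altogether, including scores already collected. A model for all available data cannot recover those scores while that sentence stands.

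**The case against.** The strongest reply is that the planned t test is a proper between-group comparison with the right error rate, and that both the Abstract and Statistical analysis tie the diet effect to it. The ANOVA is described only as an account of "evolution within each group". This stands. A reader might infer that efficacy will be claimed from within-arm p values, but the document states no such rule. The rates in Step 2 describe a misreading that the plan leaves open.

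A reader might also infer that the t test ignores baseline. The text does not say so: applied to change, it uses baseline, and at r = 0.8 the loss against ANCOVA is one point (97.5% against 98.5%). It is 12 points at r = 0.5 (69.7% against 81.6%). At r = 0.3 adjustment gains only 4 points over final values (73.7% against 69.7%). The size of the gain therefore depends on a correlation that the document does not give.

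The 50% in Step 2 is a ceiling, since 2p(1 − p) cannot exceed one half. It should not be quoted as the expected risk.

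Nor are the 1-month data unused. They can enter the within-arm ANOVA, and correlations are planned at each assessment. What is absent is a between-group use of them.

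Finally, it is tempting to argue that sequential assignment makes chance imbalance likelier and that adjustment would repair it. The document does not support that. Sequential assignment known to the researchers (Study setting) threatens selection. Adjustment deals only with imbalance in the measured baseline score.

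It might be said that all this belongs in an analysis plan not shown. But the article names the methods itself, so the point concerns a stated choice and not an omitted detail.

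**Conclusion.** The concern holds in a limited form. The between-group t test is valid but inefficient, it does not define the quantity compared, and the only longitudinal analysis cannot compare the diets. Under the stated assumptions, baseline adjustment is at least as powerful as either version of the t test at every correlation. It passes 80% power with 50 per arm from about r = 0.5, where both t tests have 69.7%.

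The interpretive risk is conditional. If within-arm p values were taken as diet effects, equal true change of 0.1 to 0.5 SD would produce significance in exactly one arm in about 16% to 50% of trials per outcome, and in the diet arm only in about 8% to 25%. This does not invalidate the trial; it is an improvement that should be made.

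**What to change.** Rewrite the Statistical analysis section as follows.

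- **Questionnaires:** a mixed model of the 1-month and 3-month scores on group, time, group-by-time and the baseline score, reporting the 3-month group difference with its 95% CI.
- **Blood markers:** ANCOVA of the 3-month value on group and the baseline value, on the log scale if skewed.
- **Within-arm change:** descriptive only, without tests.
- **Analysis set:** change the sentence that excludes participants who discontinue or deviate, so that scores already collected from them stay in the analysis under the assigned group. Without this the mixed model cannot use all available data.
- **Reporting:** state that baseline adjustment does not remove selection arising from the allocation method.

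The cost is analysis wording only. Mixed models and ANCOVA are standard procedures in the named software, and no new data are needed.
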